## Abstract

**Background:**

The NOTACS trial will assess the efficacy, safety and cost-effectiveness of high-flow nasal therapy (HFNT) compared to standard oxygen therapy (SOT) on the outcomes of patients after cardiac surgery.

**Methods/design:**

NOTACS is an adaptive, international, multicentre, parallel-group, randomised controlled trial, with a pre-planned interim sample size re-estimation (SSR). A minimum of 850 patients will be randomised 1:1 to receive either HFNT or SOT. The primary outcome is days alive and at home in the first 90 days after the planned surgery (DAH90), with a number of secondary analyses and cost-effectiveness analyses also planned. The interim SSR will take place after a minimum of 300 patients have been followed up for 90 days and will allow for the sample size to increase up to a maximum of 1152 patients.

**Results:**

This manuscript provides detailed descriptions of the design of the NOTACS trial, and the analyses to be undertaken at the interim and final analyses. The main purpose of the interim analysis is to assess safety and to perform a sample size re-estimation. The main purpose of the final analysis is to examine the safety, efficacy and cost-effectiveness of HFNT compared to SOT on the outcomes of patients after cardiac surgery.

**Discussion:**

This manuscript outlines the key features of the NOTACS statistical analysis plan and was submitted to the journal before the interim analysis in order to preserve scientific integrity under an adaptive design framework. The NOTACS SAP closely follows published guidelines for the content of SAPs in clinical trials.

**Trial registration:**

ISRCTN14092678. Registered on 13 May 2020.

**Supplementary Information:**

The online version contains supplementary material available at 10.1186/s13063-022-06607-z.

## Background

High-flow nasal therapy (HFNT) has become increasingly used as a non-invasive form of respiratory support [1]. Patients typically tolerate it better than standard alternatives such as continuous positive airway pressure or non-invasive ventilation [2]. However, there is equipoise regarding its prophylactic use and effect on important patient-centred outcomes, hence the rationale for this trial. Recent systematic reviews in non-cardiac [3] and cardiothoracic [4] surgery concluded that HFNT could reduce respiratory support and pulmonary complications, and could be safely administered.

The NOTACS (Nasal High-Flow Oxygen Therapy After Cardiac Surgery) trial will assess the efficacy, safety and cost-effectiveness of HFNT on the outcomes of patients after cardiac surgery.

This paper outlines the statistical analysis plan (SAP) for the NOTACS trial, which has been submitted for publication prior to the interim analysis to uphold scientific integrity. Further details of the study can be found in the published NOTACS protocol [5]. The NOTACS SAP closely follows published guidelines for the content of SAPs in clinical trials [6].

### Objectives

The primary objectives are to determine if prophylactic use of HFNT (for a minimum of 16 h after tracheal extubation) is clinically and cost-effectively superior in comparison with standard oxygen therapy (SOT) up to 90 days after surgery, for adult patients undergoing cardiac procedures with cardiopulmonary bypass who are at high risk of postoperative pulmonary complications. The primary objective around clinical efficacy will be evaluated by comparing DAH90 (days alive and at home in the first 90 days after the planned surgery) between the two treatment arms.

The secondary objectives are to determine if prophylactic use of HFNT is able to:Reduce mortality, pulmonary complications, intensive care re-admission rate, length of hospital and intensive care stay.Reduce incidence of major complications including sepsis, acute kidney injury, myocardial infarction and stroke.Reduce readmission to hospital rate.Improve oxygenation as measured by the ROX Index.Improve patient-centred outcomes as measured using the EQ-5D-5L.Reduce patient level of assistance needed with activities of daily living as measured using BARTHEL questionnaire.Improve quality of survival as measured using ED-5D-5L quality-adjusted life years.Reduce health service and resource use.

## Methods/design

### Design and setting

The study is an adaptive, multicentre, parallel-group, randomised controlled trial with embedded cost-effectiveness analysis comparing the use of HFNT to SOT for a minimum of 16 h after tracheal extubation, in patients at high risk of respiratory complications following cardiac surgery. Eligibility criteria and further details of the study design and setting are provided in the published study protocol [5]. Patients will be recruited from the UK, Australia and New Zealand. The NOTACS study includes an interim sample size re-estimation (SSR) which is expected to take place in late 2022, when a minimum of 300 patients have been randomised and followed up for 90 days.

### Study protocol development and conduct

The NOTACTS trial was registered with ISRCTN (ISRCTN14092678) in May 2020. The trial is overseen by a Trial Steering Committee (TSC) and a Data Monitoring and Ethics Committee (DMEC).

### Randomisation and blinding

To reduce predictability, stratified random permuted blocks will be used to randomise patients, with block sizes of 4 or 6, stratified by centre. The allocation ratio of SOT to HFNT is 1:1.

Due to the nature of the intervention, clinical staff in ICU and on the wards cannot be blinded whilst the patient is receiving randomised therapy. However, a team of research staff at the central clinical trials unit will collect data on outcomes and these staff will be blinded. In addition, the decision to discharge patients from hospital, which affects the primary outcome, will be made by clinicians who are independent of the research team at each site, according to standard protocols. The interim analysis and SSR will be done by an independent unblinded statistician so that the trial statistician can remain blinded until the final analysis in order to preserve the type I error rate at 5%.

### Data storage and collection

Data will be kept on a bespoke data management database system, OpenClinica, with blinded and unblinded access. Anonymised patient data will be provided to the statistician by the data manager.

### Primary outcome

The primary outcome for the statistical analysis is DAH90.

### Secondary outcomes

The secondary outcomes include:DAH30 (days alive and at home in the first 30 days after the planned surgery)Incidence of adverse events and serious adverse events (including death)Incidence of stroke, sepsis, acute kidney injury and myocardial infarctionPostoperative pulmonary complicationsICU re-admission rate during index admissionTotal length of ICU stay (days) during index admissionTotal length of hospital stay (days) during index admissionRe-admission to hospitalOxygenation, as measured by ROX IndexPatient-reported outcomes (EQ-5D-5L)Patient level of assistance needed with Activities of Daily Living (BARTHEL questionnaire)Quality of survival (QALYs)Health service and resource use

### Sample size calculation

Results from the pilot study [7] and information provided by collaborative hospitals were used to derive the required sample size for the NOTACS study. The sample size calculation relied on several nuisance parameters (standard deviation of DAH90 in the SOT arm; standard deviation of DAH90 in the HFNT arm; treatment switch rate from SOT to HFNT; treatment switch rate from HFNT to SOT; overall drop-out rate; overall death rate) that were provided from the single centre pilot study or collaborative hospitals and may differ between sites in the multicentre design. The sample size calculation was performed by simulation due to the non-standard distribution of the primary end-point. Due to uncertainty in the nuisance parameters used and the sensitivity of the sample size calculation to changes in the nuisance parameters, the NOTACS study includes an interim SSR, a type of adaptive design. This will provide protection against important deviations from the initial assumptions in the original sample size calculation and ensure that the study is not underpowered.

DAH90 typically has a left-skewed bi-modal distribution with a small spike at 0 due to in-hospital deaths. The required sample size was obtained by simulations (100,000 replicates) by first generating length of stay (LOS) using a lognormal distribution. Based on the information provided by collaborating hospitals, the parameters of the lognormal distributions in both arms were derived through a pooled weighted average. The variability was calibrated to SD =12.85 in the control arm and SD=3.20 in the treatment arm. The median LOS in the control arm was set to 8 days. We assumed a 3% death rate (based on pilot data [7] and registry data [8]), and following the approach of Myles [9] we treated any death within the 90-day follow-up period as scoring 90 for LOS regardless of when the death occurred. LOS was truncated at 90 days (the maximum for our follow-up period). Finally, DAH90 was computed as 90 minus LOS. The resulting data are bimodal with a spike at 0, as seen with observed data of this type.

A total sample size of 310 has 90% power to detect an increase of 2 days in the median DAH90 using the Mann-Whitney-Wilcoxon test for the analysis. After adjustment for 12% crossover from standard oxygen to HFNT and 25% crossover from HFNT to standard oxygen as well as an extra 5% loss to follow-up (equally distributed among arms), the total sample size needed to detect a 2-day increase in DAH90 with 90% power with an intention-to-treat (ITT) analysis is 850 patients.

The minimum target sample size (based on initial assumptions) is 850 randomised participants. The final sample size target will be revisited after a minimum of 300 patients have been randomised and followed up to 90 days. The adaptive design will allow for a maximum sample size increase to 1152 patients. In the event that the interim analysis recommends a sample size less than 850, recruitment will continue to the original minimum target sample size of 850.

## Statistical analysis plan

This SAP describes the statistical analyses planned for the NOTACS trial. The health economic analyses are described separately in a health economics plan.

### Statistical principles

This SAP is based on version 3.0 (19 January 2022) of the trial protocol and version 0.43 (13th June 2022) of the trial SAP. The statistical analyses will be carried out using R (www.r-project.org). Other major statistical software may be used where appropriate. Derived variables are described in the additional document. Data will be checked for outliers and unexpected distributions or data points will be queried. Consistency checks between two or more variables will also be performed. Where relevant, variables will be summarised by the treatment arm using the following descriptive statistics: for continuous variables, the non-missing sample size, mean, standard deviation, median, maximum and minimum; for categorical variables, the frequency and percentages (based on the non-missing sample size) of observed levels will be reported.

### Handling of missing data

Withdrawal rates will be summarised by the treatment arm, and the timing of and reason for withdrawals will be reported. The proportion of missing data will be quantified by the treatment group for the variables included in the primary and secondary analyses. Based on the pilot study, the rate of missing data in DAH90 is expected to be low. Variables with >25% missing data may not be used in statistical regression modelling.

The trial was powered on the basis of a 5% loss to follow-up rate. Provided there is no more than 5% missing data in DAH90 and no obvious cause for concern over the pattern of missing data then we will run complete-case analysis. If the missingness rate in DAH90 exceeds 5%, we will take further steps to investigate the type of missingness for the subset of variables included in the primary and secondary analyses. If the missing data is found not to be MCAR in any instance, we will assume the missing data is MAR and perform multiple imputation as a sensitivity analysis to evaluate the robustness of the primary analysis. Our approach to assessing missing data and implementing multiple imputation is detailed in the additional document.

For derived variables such as DAH, the presence of missing data in the variables used to calculate these from may be more difficult to identify. DAH relies on participant location diaries to capture all changes in participant location with accurate start and end dates for each change in location. There may be instances where data is missing from participant location diaries despite it appearing that the participant location diary has been completed in full, if for instances a participant fails to record a change of location. This is a potential limitation of the DAH end-point. Where it is clear that a patient diary is incomplete, they will be completed where possible by calling the patient’s GP surgery and using hospital discharge summaries.

### Patient flow

The participant timeline can be found in the study protocol [5]. A CONSORT diagram will be produced as part of the statistical analysis to show the flow of patients through the study, from recruitment through to treatment allocation, discharge, 30 days and 90 days follow-up.

### Analysis populations

Each patient will be included or excluded from each of the analysis populations defined below. This will be carried out prior to unblinding to avoid bias.

#### Safety population

The safety population includes all subjects entered into the trial from the time of tracheal extubation up to 90 days after surgery (the period for which safety data is being collected) at the time of database lock. The safety population will be used to provide summary statistics on adverse events (AEs) and serious adverse events (SAEs), which will be reported by the treatment arm assigned during randomisation (or by the treatment arm actually received if it is different to that assigned during randomisation). The safety population will be examined at both the interim and final analyses. It will include patients with partial data as well as any patients who have withdrawn from the trial provided they continue to consent to their data being used.

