### Interim analysis

The interim analysis will be performed after a minimum of 300 patients have been randomised and followed up for 90 days. If there is greater than 15% missing data for DAH90 (excluding missingness because of death, which is informative missingness) then the interim analysis may be delayed. If at the time 300 patients have been randomised and followed up, the rate of UK participation is outside the target range, the interim analysis may be delayed as per the definition of the interim analysis population.

Three main areas will be examined at the interim analysis:SafetyRecruitment, compliance and data completenessSSR

The safety analyses at the interim analysis will be identical to the safety analyses at the final analysis, described below. Information on recruitment, treatment compliance, and data completeness will be reported at both the interim and final analysis. A summary of patient recruitment data will be presented by the centre, as well as by the treatment group and time or trial stage where appropriate. Compliance and data completeness will be summarised by the treatment group.

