### Safety analyses

All safety analyses will be performed on the safety population. Data on AEs and SAEs will be collected from the time of tracheal extubation to discharge. From discharge up to 90 days after surgery, only data on SAEs will be collected. Adverse events (AEs) and serious adverse events (SAEs) will be summarised separately. AE and SAE data will be listed by MedDRA Preferred Term and further grouped by System Organ Class. The frequencies of the AEs will be summarised by treatment groups. Death, stroke, sepsis, myocardial infarction and acute kidney injury are SAEs of special interest. Therefore, the rates of these will be estimated for each treatment group separately to the main SAE summary table.

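### Death and the major complications are secondary objectives, yet the only analysis stated for them groups patients by treatment received, so it loses the protection of randomisation, with bias possible in either direction

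*SAP article*

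**What the plan says.** The Safety population section (under Analysis populations) has AEs and SAEs summarised by the assigned arm, "or by the treatment arm actually received if it is different to that assigned during randomisation". The Safety analyses section then says "All safety analyses will be performed on the safety population". It adds that "Death, stroke, sepsis, myocardial infarction and acute kidney injury are SAEs of special interest", and that "the rates of these will be estimated for each treatment group separately to the main SAE summary table". For the interim, the Interim analysis section states: "The safety analyses at the interim analysis will be identical to the safety analyses at the final analysis".

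The same events appear as efficacy aims. The Objectives section includes "Reduce mortality, pulmonary complications, intensive care re-admission rate, length of hospital and intensive care stay" and "Reduce incidence of major complications including sepsis, acute kidney injury, myocardial infarction and stroke". The list of secondary outcomes under Methods/design repeats them, with death placed under serious adverse events.

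The section on secondary outcomes under Analysis for secondary endpoints assigns tests or models to DAH90, DAH30, ICU stay, the ROX index, countries and UK centres, extubation timing and return to theatre. It assigns none to death, stroke, sepsis, MI or AKI.

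On switching, the Sample size calculation section reads "After adjustment for 12% crossover from standard oxygen to HFNT and 25% crossover from HFNT to standard oxygen".

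**The concern.** Randomisation makes the arms comparable as assigned. Once patients are regrouped by the therapy they ended up with, any link between switching and prognosis enters the comparison. For tolerability listings that is an accepted price. For outcomes that the trial set out to reduce, it means the stated rates do not answer the objective.

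Three features add to this:

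- Planned crossover is substantial and unequal in the two directions.
- Treatment received is not defined for a patient who had both therapies, so the size of the regrouping depends on a rule that the article does not give.
- The safety population, and AE/SAE collection, begin at tracheal extubation. The Intention-to-treat population section scores a death between randomisation and extubation as zero days at home. Such a death therefore counts in the primary analysis but not in the per-arm death rates, and the two will not reconcile.

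The last feature also matters because the Analysis for the primary endpoint section justifies scoring deaths as zero partly by expecting similar mortality in the two arms. The planned death rates cannot check that expectation for the arms as randomised.

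**Working it through.** **Inputs from the article.** 1:1 allocation; N = 850 (minimum target) and 300 (minimum at interim); crossover a = 0.12 (SOT to HFNT) and b = 0.25 (HFNT to SOT); death rate d = 0.03.

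**Assumed, because the article gives no figure.** kS is the death risk of SOT-to-HFNT switchers relative to SOT patients who do not switch. kH is the same for HFNT-to-SOT switchers. There is no true treatment effect, and every switcher is moved.

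**The plan's own figures.** The crossover rates were checked against the sample size they produce. The simulation used 3,000 replicates of lognormal stay with median 8 and SD 12.85 (SOT) or median 6 and SD 3.20 (HFNT), truncated at 90, with 3% deaths set to 90 and a Mann-Whitney-Wilcoxon test at 5% (two-sided assumed). Power was 90.7% at N = 310 without crossover, and 90.4% at N = 850 with random 12%/25% crossover and 5% loss. The Monte Carlo standard error is about 0.5 points. Both stated sizes reproduce at 90% power.

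**How many patients could move.** At N = 850 there are 425 per arm.

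- SOT to HFNT: 0.12 × 425 = 51.
- HFNT to SOT: 0.25 × 425 = 106.25.
- Total: 157.25, or 157.25/850 = 18.5%.
- Groups by treatment received: SOT 425 − 51 + 106.25 = 480.25; HFNT 425 − 106.25 + 51 = 369.75.

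**Death rates by treatment received under no effect.** Each randomised arm is held at 3%:

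- s0 = d/(1 − a + a·kS) for SOT non-switchers, and s1 = kS·s0 for switchers.
- h0 = d/(1 − b + b·kH) for HFNT non-switchers, and h1 = kH·h0 for switchers.
- HFNT received = [(1 − b)·h0 + a·s1]/0.87.
- SOT received = [(1 − a)·s0 + b·h1]/1.13.

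kS = 3, kH = 1: s0 = 0.03/1.24 = 0.02419 and s1 = 0.07258. HFNT = (0.0225 + 0.00871)/0.87 = 3.59%. SOT = (0.02129 + 0.0075)/1.13 = 2.55%. Ratio 1.41.

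kS = 1, kH = 3: h0 = 0.03/1.50 = 0.02 and h1 = 0.06. HFNT = (0.015 + 0.0036)/0.87 = 2.14%. SOT = (0.0264 + 0.015)/1.13 = 3.66%. Ratio 0.58.

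| kS | kH | HFNT received | SOT received | Risk ratio |
|---|---|---|---|---|
| 1 | 1 | 3.00% | 3.00% | 1.00 |
| 2 | 1 | 3.33% | 2.75% | 1.21 |
| 3 | 1 | 3.59% | 2.55% | 1.41 |
| 5 | 1 | 3.98% | 2.24% | 1.78 |
| 5 | 0.5 | 4.35% | 1.96% | 2.22 |
| 3 | 3 | 2.73% | 3.21% | 0.85 |
| 1 | 3 | 2.14% | 3.66% | 0.58 |

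By randomised arm, every row gives 0.03 × 425 = 12.75 expected deaths per arm and a ratio of 1.00.

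**At the interim.** With N = 300, 0.12 × 150 = 18 and 0.25 × 150 = 37.5 patients could move, and 0.03 × 300 = 9 deaths are expected in total. With kS = 3 and kH = 1 the split by treatment received is about 4.7 (HFNT) to 4.3 (SOT), against 4.5 each by randomised arm.

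**The case against.** **The direction is unknown.** A reader might infer that the rule loads bad outcomes onto HFNT. The documents do not support that. The larger planned flow is from HFNT to SOT, the article gives neither reasons for switching nor switchers' risk, and the table runs from 0.58 to 2.22. This stands: no direction can be claimed.

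**Treatment received may be narrow.** Assigned arm comes first in the rule, and the exception may cover only patients who never had their allocated therapy. Few would then move, and the bias would be small. This also stands, so 157 is an upper figure for the planned rates. It does not rescue the text, which does not say which reading applies.

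**The article is condensed.** It names no analysis for several other secondary outcomes, it refers to a fuller SAP and an additional document, and it says that intention to treat (ITT) serves most analyses. A reader should therefore not conclude that the full plan lacks an ITT mortality comparison. The point made here concerns a grouping rule that is written down and applied explicitly to all safety analyses, including these events.

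**Deaths are already in the ITT primary analysis, and the safety output is descriptive.** Both are true. But a rank test on DAH90 does not isolate mortality, and descriptive rates will still be read against an objective of reducing these events.

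**Reporting by treatment received is conventional, and starting at extubation is coherent.** Both are reasonable for safety of a therapy given after extubation. Neither suits the sole stated analysis of an efficacy objective. The number of deaths before extubation is not given and may be small.

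**The interim harm is speculative.** A reader might infer that the monitoring committee would see a false signal. The article says only that the updated sample size is reported to it. That the safety tables go there too is a reasonable inference, but with about 9 deaths the shift in the case shown is a fraction of one death. No stronger claim is justified.

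**Conclusion.** The point holds in a limited form. As written, the only analysis that the article states for death, stroke, sepsis, MI and AKI as outcomes in their own right groups patients by treatment received where it differs from assignment, although reducing these events is a secondary objective. With the planned crossover, up to 18.5% of patients could change group.

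Under no true effect the expected death risk ratio is then 1.00 only if switching is unrelated to prognosis or the two flows happen to cancel. It is 1.41 or 0.58 when one type of switcher has three times the risk. These ratios rest on assumed switcher risks, 3% mortality in each arm and every switcher being moved. They show that the comparison is unprotected; they do not predict a result.

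Separately, deaths between randomisation and extubation are missing from the per-arm death rates while they score zero in the primary analysis.

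**What to change.** At both the interim and the final analysis:

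- Report death by randomised arm in all randomised patients, including deaths before extubation.
- Report stroke, sepsis, MI, AKI and SAEs by randomised arm, using the events already collected from extubation onwards. Non-fatal events before extubation are outside the stated collection window, so a table of these events covering the whole period from randomisation would need new data and is not asked for.
- Keep the table by treatment received as a supplement, labelled as such.
- Define treatment received for patients who had both therapies.

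The cost is a change of SAP wording and one extra table set. Deaths from randomisation are already needed for DAH90, and the sample size does not change.
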